Two knowledge gaps can be identified in the evidence for CT control strategies. First, we do not understand the role of anorectal CT in women in overall CT spread. In women, anorectal infections are about as common as genital infections, with proportions positive ranging between 7 - 27 % of anorectally tested women [13-25]. Yet, most anorectal CT infections remain undetected as general practitioners, hospital and population testing initiatives ignore anorectal CT and largely focus on genital CT [26]. STI clinics do test women at the anorectal site on indication, i.e., when they report anal sex or symptoms. Still, with half of all anorectal CT occurring in women who do not report anal sex, many anorectal infections are left untested. Second, we do not know whether transmission of CT can occur in the weeks following currently recommended treatment. Prior studies have shown considerable detection of both anorectal and genital CT after treatment in women and men [27–32]. Detection rates depended on the number of samples taken and type of tests used, demonstrating up to 40 % of treated cases having at least one positive sample when sampled multiple times within 8 weeks [27]. Indeed, repeat genital CT infections are common following treatment, varying between 10 % and 30 % when re-testing CT positive treated women between 3 months and a year later [33]. Guidelines advise such re-screening at 3 months after a CT diagnosis. Yet, in practice, re-screening occurs in less than a third of patients in the Netherlands [34]. Current care does not include a routine re-test of patients within 3 months of treatment [35-37] nor does it include an anorectal re-test 3 months after the genital CT treatment. Many uncertainties exist on the clinical relevance of a post-treatment CT detection. It is unknown whether it reflects transmission after sexual exposure or self-infection. It is also unknown whether detection of CT nucleic acids indicates viable or nonviable CT and what organism loads are present [38]. Suboptimal treatment may possibly play a role, but evidence is inconclusive leading to considerable debate on this issue [39–42].

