### Collection of self-reported data

Data will be collected by online self-administered questionnaires at inclusion, and during follow-up around the sampling times. The questionnaire at inclusion contains questions on age, ethnicity, gender, socio-economic status. All questionnaires contain questions on number of partners, and for each sexual partner the sexual behaviour (genital, anal, oral sex) in the past two weeks, testing for STI and treatment. It also includes questions on behaviours such as contraceptive use, antibiotic use, drug use, STI testing during follow-up, and on list of symptoms. Further, participant data will be collected concerning treatment type and compliance. For the purpose of process evaluation, a few questions are included that address acceptability and possible difficulties encountered related to the participation in the study. Each participant has a study code under which all data (samples and questionnaires) are collected and analysed.

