### Definition of transmission

Transmission is defined as an observed incident CT detection post-treatment (a) after having sex with a source partner (by self-reported behaviour and biomarker-validation), and (b) when another anatomical source location tested positive, i.e., self-infection. In such cases, self-infection is considered likely when CT strain types do not differ between anatomic sites of a woman. Samples with CT detection that follow a sample with CT detection may represent persistence and are considered not indicative for transmission. In such cases, persistence is considered likely when CT strain types do not differ in a woman over time.

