### Defining sexual exposure

In women, the process of CT acquisition from an infected partner, i.e., via sex, is defined based on sexual behaviour data from the detailed and frequent questionnaires and by biomarker assessment. The actual CT status of the partner during follow-up will in most cases be unknown. Hence, the sexual behaviour that is reported during follow-up may also include sex with CT negative partners. The risk estimate for the association between sexual exposure and incident CT detection reflects the risk of transmission given this sexual practice and regardless of the partner's CT status. This will be a good proxy to the actual transmission probability for a given sexual practice in ‘real life’ and is most relevant in the practical care setting where information on sexual behaviour is routinely asked about and registered and partners’ CT status is often lacking. To validate sexual exposure from a man, especially to indicate underreporting, biomarker validation is applied.

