### Statistical analyses

The main study questions will be answered by analysing the data on the level of episodes. For each incident CT detection, the information of the preceding sample results, and the sexual behaviour information from the preceding 2-week interval, is analysed. Using mixed models, univariate and multivariate logistic regression analyses will be applied to calculate rates of incident CT anorectal and genital detection, controlling for repeated measurements in a person. Thereby, the relative contributions are assessed of sexual exposure and of alternate anatomic site exposure, i.e., sexual transmission and self-infection. This will be done by including different exposures as co-factors and this will also be done comparing categories of sexual exposure, anatomic site exposure, and both exposures compared to no such exposure (see Table 2).

**Table 2 Tab2:** Main regression models in FemCure study

	Exposure categories	Definition in the data^b^	Interpretation^c^ of positive CT test result
Outcome incident genital CT detection			
Model 1	Sexual exposure^a^	Genital sexual exposure (at T_x_)	
	Alternate site exposure	Anorectal CT positive (at T_x_ and/or T_x-2_)	
Model 2	No exposure	No genital sexual exposure (at T_x_) AND anorectal CT negative (at T_x_ and T_x-2_)	Persistence
	Genital sexual exposure only	Genital sexual exposure (at T_x_) AND anorectal CT negative (at T_x_ and T_x-2_)	Sexual transmission
	Anorectal site exposure only	No genital sexual exposure (at T_x_) AND anorectal CT positive (at T_x_ and/or T_x-2_)	Transmission from anorectal site
	Sexual exposure and anorectal site exposure	Genital sexual exposure (at T_x_) AND anorectal CT positive (at T_x_ and/or T_x-2_)	Sexual transmission AND/OR Transmission from anorectal site
Outcome incident anorectal CT detection			
Model 1	Sexual exposure^a^	Anorectal sexual exposure (at T_x_)	
	Alternate site exposure	Genital CT positive (at T_x_ and/or T_x-2_)	
Model 2	No exposure	No anorectal sexual exposure (at T_x_) AND genital CT negative (at T_x_ and T_x-2_)	Persistence
	Anorectal sexual exposure only	Anorectal sexual exposure (at T_x_) AND genital CT negative (at T_x_ and T_x-2_)	Sexual transmission
	Genital site exposure only	No anorectal sexual exposure (at T_x_) AND genital CT positive (at T_x_ and/or T_x-2_)	Transmission from genital site

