	Sexual exposure and genital site exposure	Anorectal sexual exposure (at T_x_) AND genital CT positive (at T_x_ and/or T_x-2_)	Sexual transmission AND/OR Transmission from genital site

^a^Based on self-administered questionnaires and semen biomarker assessment

^b^T_x:_ test result at the sampling; T_x-2:_ test result at the sampling two weeks earlier

^c^Strain typing is used to further aid interpretation of the observed positive CT test result, specifically to confirm self-infection (i.e., strain types do not differ between anatomic sites) or persistence (i.e., strain types do not differ over time)

Risks will be expressed by odds ratio‘s and 95 % confidence intervals. Co-factors (such as age, but also treatment-type) will be included in the models to account for their potential role as a confounding factor or effect-modifier in the associations between exposure and CT detection. Also, these co-factors are assessed for their association with CT detection.

Sensitivity analyses will be undertaken by varying the definition of the outcome (primary and secondary outcomes) and by varying the definition of the sexual exposure (e.g., including and excluding sexual practices). By performing a (limited) process evaluation of our study, we will obtain insights in the factors that have affected participation and possible loss-to-follow-up.

In a sub analysis, in which the unit of analysis will be an individual woman (not the 2-week episodes), a head-to-head comparison of the two treatments will be conducted.

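### The anorectal models count vaginal-sex-only episodes as unexposed, so a new anorectal detection after vaginal sex is read as persistence or self-infection

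*Protocol article*

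**What the plan says.** Table 2 in *Statistical analyses* sets out two main models per outcome. In each, sexual exposure is a single present/absent term matched to the outcome site: genital sex for genital CT, anorectal sex for anorectal CT. A footnote gives its source: "Based on self-administered questionnaires and semen biomarker assessment".

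The reference category of anorectal Model 2 is "No anorectal sexual exposure (at T_x_) AND genital CT negative (at T_x_ and T_x-2", and a positive test in it is interpreted as persistence. The genital counterpart is "No genital sexual exposure (at T_x_) AND anorectal CT negative (at T_x_ and T_x-2", with the same interpretation.

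Three other places bear on this:

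- *Background* describes anorectal CT "with half of all anorectal CT occurring in women who do not report anal sex".
- *Collection of self-reported data* says the questionnaires record "for each sexual partner the sexual behaviour (genital, anal, oral sex) in the past two weeks, testing for STI and treatment".
- *Statistical analyses* plans sensitivity analyses that vary the definition of sexual exposure. Including or excluding practices is given as an example, and the content is not fixed further.

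**The concern.** The study wants to separate sexual transmission from self-infection and to weigh the two against each other. For the anorectal outcome, the only sexual route the main models recognise is anal sex. A woman who had vaginal but not anal sex in the interval counts as sexually unexposed, whatever her contact with a partner.

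Two things are at stake. The first is the label: an anorectal detection that followed vaginal sex is reported as persistence or as spread from the genital site. The second is the odds ratio for anal sex, because its comparison group mixes episodes with no sex and episodes with vaginal sex. By the protocol's own account, about half of anorectal infections arise in women who report no anal sex, so the group concerned is not marginal.

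**Working it through.** **Step 1: where episodes fall in anorectal Model 2.**

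| Sex in the interval | Genital tests (current and previous sampling) | Cell | Printed reading of a new anorectal positive |
|---|---|---|---|
| None | Both negative | No exposure | Persistence |
| Vaginal only | Both negative | No exposure | Persistence |
| None | At least one positive | Genital site only | From genital site |
| Vaginal only | At least one positive | Genital site only | From genital site |
| Anal, with or without vaginal | Both negative | Anorectal sex only | Sexual transmission |
| Anal, with or without vaginal | At least one positive | Both exposures | Either or both |

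No cell lets a detection after vaginal sex alone be read as sexual transmission. In the genital models, anal sex without vaginal sex is likewise placed under no genital sexual exposure.

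**Step 2: inputs for the size.** The article gives no figure that settles it. *Numbers and power* gives reported sex in 20-60% of two-week episodes, not split by practice, and no effect size. The rest is assumed, as an illustration with one observation per episode and no random effects.

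- v: share of reference episodes with vaginal sex, 20%, 40% or 60% (borrowed from the range for any sex)
- p0: detection risk without sex, 5% or 15%
- True odds ratio against no sex: 1 to 3 for vaginal sex, 3 for anal sex

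Formulas, with odds(p) = p/(1−p):

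- Reference risk: p_ref = v·p_vag + (1−v)·p0
- Planned odds ratio: odds(p_anal)/odds(p_ref)
- Share of reference detections in excess because of vaginal sex: v·(p_vag − p0)/p_ref

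**Step 3: one case in full.** Take p0 = 5%, v = 40% and a vaginal odds ratio of 2.

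- odds(p0) = 0.0526, so p_vag = 0.1053/1.1053 = 0.0952.
- p_ref = 0.4 × 0.0952 + 0.6 × 0.05 = 0.0681, with odds 0.0731.
- odds(p_anal) = 3 × 0.0526 = 0.1579.
- Planned odds ratio = 0.1579/0.0731 = 2.16.
- Anal sex against no sex is 3.0; against vaginal sex it is 3/2 = 1.5. The planned value lies between them.
- Excess share = 0.4 × 0.0452/0.0681 = 27%.

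**Step 4: the range**, over both values of p0 and vaginal odds ratios from 1.5 to 3. The true odds ratio of anal sex is 3.0 against no sex and 3/1.5 = 2.0 down to 3/3 = 1.0 against vaginal sex.

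| v | Planned anal-sex odds ratio | Excess detections read as persistence |
|---|---|---|
| 20% | 2.2-2.7 | 7-26% |
| 40% | 1.7-2.5 | 14-41% |
| 60% | 1.4-2.3 | 19-51% |

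With a vaginal odds ratio of 1 the planned value is 3.0 and the excess is zero.

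**Step 5: low background risk, anal sex adding nothing over vaginal sex.** Assume any sex in 40% of episodes, anal sex in 10%, risk 1.5% without sex and 4.5% after any sex.

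- Vaginal-only share of the reference: 30/90 = 1/3.
- p_ref = (1/3) × 4.5% + (2/3) × 1.5% = 2.5%.
- Planned odds ratio: 0.0471/0.0256 = 1.8.
- Against no sex: 0.0471/0.0152 = 3.1.
- Against vaginal sex: 1.0.

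**The case against.** The strongest objection concerns the route. The reference cell requires negative genital tests at both samplings. If vaginal sex reaches the anorectum only by first causing a detected genital infection, the alternate-site term captures it and the reference group is not contaminated. The Background figure of one half describes anorectal CT in general, says nothing about route, and is as compatible with self-infection. The Background also says that 75-95% of anorectal CT co-occurs with genital CT, so many such cases would fall outside the reference cell. All this stands: the size is unknown and may be zero. But the printed labels take that answer as given, when the route is what the study is meant to investigate.

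Second, safeguards exist. The sensitivity analysis could move vaginal sex out of the reference group, the co-factor list is open, and strain typing and the semen biomarker can correct some labels. These help only in part. The sensitivity analysis is not fixed and leaves the main models as they are. Table 1 limits typing and the biomarker to a subset. An unchanged strain does not exclude reinfection by the same untreated partner.

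Third, a reader might infer that pooling all partners is also an error, because *Definition of transmission* speaks of detection "after having sex with a source partner" while *Defining sexual exposure* accepts that "the sexual behaviour that is reported during follow-up may also include sex with CT negative partners". The documents do not support that. The latter section explains the pooling: partner status is mostly unknown, and the estimate is meant for routine care. Partner treatment could still enter as a co-factor. An infected partner shared by both sites could in principle create an apparent site-to-site association, but its size depends on acquisition and clearance rates that the article does not give, so no figure is attached here.

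**Conclusion.** The point holds for the classification, which follows from Table 2 alone: vaginal-sex-only episodes sit in the anorectal reference group, and the main model cannot credit a detection in them to a partner.

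The effect on the estimates is conditional. If vaginal sex carries anorectal risk without genital detection, the planned anal-sex odds ratio falls between two meaningful contrasts and equals neither. A reader might infer that the anal-sex effect is simply overstated. That is true only of its added effect over vaginal sex; against no sex it is understated. Under the assumed inputs of the range table, 7-51% of reference-group detections would be excess due to vaginal sex yet read as persistence. These figures show what is possible and do not predict what the study will find.

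This is a cheap improvement to the main models and does not undermine the design.

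**What to change.** - In the main anorectal models, include both vaginal and anal exposure. Define no exposure as neither practice and add a vaginal-sex-only category. Report anal sex both against no sex and against vaginal sex only.
- Include anal sex in the genital models in the same way.
- Do not read a detection in the current reference cell as persistence when any sex was reported in the interval.
- Keep the pooled any-partner estimate as the main one. A split by reported partner testing or treatment is an optional additional analysis.

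The questionnaires already record each practice for each partner, so no new data are needed. The cost is one or two extra parameters per model and smaller cells, hence wider confidence intervals.

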**Methods:**

A multicentre prospective cohort study (FemCure) is set up in which genital and/or anorectal CT positive women (*n* = 400) will be recruited at three large Dutch STI clinics located in South Limburg, Amsterdam and Rotterdam. The women self-collect anorectal and vaginal swabs before treatment, and at the end of weeks 1, 2, 4, 6, 8, 10, and 12. Samples are tested for presence of CT-DNA (by NAAT), load (by quantitative polymerase chain reaction -PCR), viability (by culture and viability PCR) and CT type (by multilocus sequence typing). Sexual exposure is assessed by online self-administered questionnaires and by testing samples for Y chromosomal DNA. Using logistic regression models, the impact of two key factors (i.e., sexual exposure and alternate anatomic site of infection) on detection of anorectal and genital CT will be assessed.

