### Defining alternate anatomic site exposure

The process of CT anorectal acquisition from her own genital CT infection and vice versa is defined based on the CT test results. Exposure is defined as presence of CT detection at the other anatomic site at the same sampling moment and/or the previous sampling moment. CT typing results are also used to confirm the link between the two detections.

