### Limitations

First, it cannot be ruled out that some degree of misclassification in both exposures and outcomes may occur. Sexual exposure may be underreported, even when validity and reliability of the questionnaire data are optimized and biomarker validation is applied (exposure misclassification). Also, a woman may clear the CT infection before the sampling occurs (outcome misclassification). However, an even more frequent sampling as already scheduled (at weeks 0,1,2,4,6,8, 10, and 12) was considered to potentially compromise study inclusion and retention and would also require more funds than are currently available.

Second, a randomised controlled trial (RCT) would be the most suited study design to compare efficacy of treatments, such as recently reported for genital CT [48]. The observational FemCure study is not designed as an RCT as a treatment comparison is not its main aim and an RCT would require more human and financial resources than are currently available. Nevertheless, the role of treatment can and will be evaluated in a sub-analysis by a head-to-head comparison of treatment-types. Most of the current studies reporting comparison of anorectal CT treatments similarly are observational studies with inherent biases to account for [28–32, 39–41]. By including different anatomic sites and a diverse range of laboratory and exposure measures in the current study, results will add to the existing literature and will thereby be able to inform the current debate on treatment failure.

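### The two definitions of alternate-site exposure conflict at weeks 1 and 2, and each counts the pre-treatment swab as an exposure at one post-treatment sample

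*Protocol article*

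**What the plan says.** Alternate-site exposure is one of the two key exposures in every main model. Table 2 (Statistical analyses) scores a woman as exposed if the other site is positive at the index sampling, at T_x-2, or at both. Footnote b explains T_x-2 as the "test result at the sampling two weeks earlier". The section Defining alternate anatomic site exposure gives a different rule for the same variable: detection at the other site "at the same sampling moment and/or the previous sampling moment".

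The swabs are collected "before treatment, and at the end of weeks 1, 2, 4, 6, 8, 10, and 12" (Abstract, Methods); Table 1 and Limitations give the same schedule. For each incident detection, the results of preceding samples and "the sexual behaviour information from the preceding 2-week interval, is analysed".

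Under Definition of transmission, a detection that follows another detection is treated as possible persistence and not as transmission. The article does not say which lag decides this. Table 2 reads a detection with neither exposure as persistence, and a detection with only the other site positive as transfer from that site. Nothing in the article bars the pre-treatment swab (T0) from serving as an exposure, or weeks 1 and 2 from serving as outcomes.

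**The concern.** A fixed two-week lag suits samples that are two weeks apart. The first three samples are one week apart, so the fixed lag and the previous-sample rule diverge exactly where the schedule changes. At one early sample, whichever rule is followed, the lag falls on a swab taken before treatment.

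The study asks about transmission after treatment. A positive T0 swab shows that the other site was infected before treatment. It does not show that the site was still a source afterwards. Because women enter with infection at one or both sites, exposure defined by T0 is close to universal, so that episode offers little or no contrast. A detection there may then be credited to self-infection although the infection at the index site may simply have persisted.

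**Working it through.** **Inputs.** Sampling weeks 0, 1, 2, 4, 6, 8, 10, 12, with week 0 before treatment (Abstract; Table 1; Limitations). Lag rules from Table 2 footnote b and from Defining alternate anatomic site exposure. Eligibility requires genital and/or anorectal infection, and 75% are expected to have both (Study population). Planned recruitment is 400 (Numbers and power).

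**Step 1: apply each rule to each post-treatment sample.**

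| Sample week | Footnote b (week minus 2) | Text rule (previous sample) |
|---|---|---|
| 1 | week −1: no sample | week 0, pre-treatment |
| 2 | week 0, pre-treatment | week 1 |
| 4 | week 2 | week 2 |
| 6 | week 4 | week 4 |
| 8 | week 6 | week 6 |
| 10 | week 8 | week 8 |
| 12 | week 10 | week 10 |

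The rules disagree at weeks 1 and 2 and agree at the other five samples. Each reaches T0 exactly once: 1/7 = 14%.

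**Step 2: see whether the choice changes the reading.** Take a woman who is anorectally positive at T0 and negative at weeks 1 and 2, genitally negative at week 1 and positive at week 2, and who reports no genital sex. Let incident mean negative at the sample just before. Footnote b places her in the category with anorectal exposure only, read as transfer from the anorectal site. The text rule places her in the category with no exposure, read as persistence. The same data give two different answers.

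**Step 3: share exposed at week 2 under footnote b.** This depends on what incident means.

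- *Incident means index site negative at week 1.* The share of all women exposed through T0 is 75% (both sites) plus those positive only at the other site, so at least 75% in either model. At most 25% remain unexposed, or 0.25 × 400 = 100 women, before removing those positive at the other site at week 2 itself. These are shares of all women; the share among women at risk is not known.
- *Incident means index site negative at T0.* Eligibility requires at least one positive site, so the other site is positive and 100% of women at risk are exposed. The group at risk is itself small: at most 25% of women, or 100 of 400, have a single infected site. Most of them are expected to be genital only and so belong to the anorectal model.

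**Step 4: share exposed at week 1 under the text rule.** Women negative at the index site at T0 are positive at the other site by the same argument: 100%.

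The 100% figures assume that the T0 study swabs agree with the routine result that made the woman eligible.

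**Step 5: sexual exposure window.** With a two-week recall, the window at week 2 runs from week 0 to week 2. Half of it lies before the week 1 sample that would serve as the lag under the text rule.

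**The case against.** The strongest reply is that week 1 was probably never meant to be a model episode. The analysis is described in two-week episodes, and the week 1 questionnaire covers sexual behaviour only briefly (Table 1, footnote d). On a grid of weeks 2, 4, 6, 8, 10 and 12, footnote b always finds a sample and the recall window matches the lag. This is plausible and removes the week 1 difficulty, but the article does not state it, and the first episode on that grid would still use T0.

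Other points have partial force. Definition of transmission requires the detection, not the source result, to be post-treatment, so T0 is not expressly excluded; it still says little about a source after treatment. Viability is measured after treatment only at weeks 4, 8 and 12, so a viability outcome avoids weeks 1 and 2, but the primary NAAT outcome does not. Women who also report sex fall in a mixed category, so not every such detection is read as self-infection alone. Strain typing is done in a subset, and an unchanged strain is taken to support both self-infection and persistence. The planned sensitivity analyses vary the outcome and the sexual exposure, not this lag.

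Three stronger readings are tempting and not supported:

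- That two of seven samples (29%) are contaminated by T0. This adds together two rules that cannot both apply; each reaches T0 once.
- That the high exposure contradicts the 10–30% in the power scenarios. That range is not specific to a week. If all women were at risk in six episodes, 75% at week 2 and 10% in the other five would pool to (0.75 + 5 × 0.10)/6 = 21%, inside the range.
- That more exact shares can be given for each site. The documents do not split the remaining 25% into genital only and anorectal only.

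**Conclusion.** The point holds as a conflict between two stated definitions of a key exposure, confined to weeks 1 and 2. Under either rule, one of seven post-treatment samples (14%) scores the treated baseline infection as alternate-site exposure. In that episode the unexposed group is at most about 25% of all women, or absent among those at risk, given the plan's expected 75% with both sites infected, the eligibility rule, and T0 swabs that agree with the routine result.

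Misreading persistence as transfer is clearest at week 2 when incident means negative at week 1, because most women were positive at both sites at T0. Where women at risk were negative at the index site at T0, persistence would require a missed infection, and the main problem is the lack of any comparison group.

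A reader might infer that the main models as a whole are invalid. They are not shown to be: weeks 4 to 12 are the same under both rules. How far the one episode would move the pooled odds ratios cannot be worked out, because the article does not give the numbers at risk by week.

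**What to change.** - Use a single rule in Table 2, footnote b and Defining alternate anatomic site exposure: the lag is the immediately preceding post-treatment sampling. Apply the same lag to define an incident detection.
- State that T0 is not used as an exposure.
- Exclude week 1 as an outcome from the transmission models and start them at week 2 with week 1 as the lag. Keep week 1 for the descriptive detection rate.
- Report a sensitivity analysis starting at week 4. The two-week recall cannot isolate sexual exposure in the single week between the week 1 and week 2 samples.

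This changes wording and one derivation rule and needs no new data. The cost is slightly fewer early episodes in the models.
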